## 10. Research methodology

### 10.1 Population

Postpartum women aged 15 to 19

### 10.2 Sample

The study sample consisted of postpartum women aged 15 to 19 who were admitted to the general obstetrics ward, Queen Savang Vadhana Memorial Hospital, Thai Red Cross Society, Thailand.

### 10.3 Sample size estimation

The sample size for this study was determined using G\*Power (version 3.1.9.4), the effect size indicated a large effect (Cohen's guidelines), a power of test equal to 0.80, and a significance level set at 0.05. The analysis indicated that a sample size of 26 participants per group. To account for dropouts of 10 percent, the final sample was 30 participants per group. Consequently, the total sample size was established at 60 participants.

### 10.4 Inclusion criteria

1. Full-term deliveries (37-42 weeks)
2. Postpartum women aged 15 to 19
3. Mother without postpartum complications such as postpartum hemorrhage, preeclampsia with severe features, etc.
4. Infants exhibited no severe complications or congenital anomalies necessitating NICU admission or separation from the mother.
5. Mother intended to childcare for six-week
6. Participants could read, write, and communicate in Thai.
7. Demonstrated the ability to communicate via mobile using the LINE application.

### Exclusion criteria

1. The participant did not personally care for the infant for the entire six-week postpartum period.
2. The participant was unable to complete all phases of the study.
3. The participant chose to withdraw from the research.

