Effective support for adolescent mothers requires nurses to cultivate a positive attitude and maintain open communication, thereby facilitating an accurate understanding of each mother's needs. Such rapport can alleviate maternal anxiety and foster adaptation to the maternal role (Erfina et al., 2019; Intrakasem et al., 2019). Care should emphasise role adjustment through education, hands-on skill-building in infant care and breastfeeding, and structured activities that strengthen the mother–infant bond, all of which promote maternal confidence. Because adolescents are frequent users of digital technology, integrating social media and other online platforms into postpartum care represents an essential component of contemporary service models (Mekkamon & Wichienprapha, 2018). Current postpartum practice, however, often falls short of these ideals. Routine hospital discharge within 2–3 days limits opportunities for comprehensive and continuous skill development, and most institutions provide no structured follow-up or communication system after discharge, relying instead on printed manuals for self-study. This discontinuity may heighten anxiety and undermine caregiving effectiveness once mothers return home.

A review of the literature, corroborated by the researcher's clinical experience, indicates that postpartum care for adolescent mothers remains largely indistinguishable from that offered to adult mothers. Instruction is typically delivered through lectures, demonstrations, and brief skills training sessions. Yet adolescent mothers are seldom provided with accessible, engaging resources for later review: most information is still distributed as manuals, pamphlets, or compact discs, formats that neither match adolescents' media preferences nor sustain their attention. Opportunities for convenient follow-up consultation are likewise scarce. Accordingly, this study seeks to design and evaluate a technology-enhanced care model tailored to the specific needs of adolescent mothers.

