### 10.6 Instrument

#### 10.6.1 Instruments for implementation

1. **The parental enhancing program**, developed by the researcher, is based on Belsky's "A Process Model of Competent Parental Functioning". The program consists of the following activities:

- Session 1 (24-48 hours postpartum): Establishes rapport and strengthens the mother-infant bond. The researcher provides personalized knowledge and skills training on recognizing infant cues and responsiveness, general infant care, breastfeeding techniques, bathing procedures, and identifying abnormal symptoms in infants, lasting about 60 to 90

minutes. Teaching materials, such as infographics, e-books, and instructional videos, are disseminated through the 'Line Official Account™ Parent Paplearn' as a mobile application.

- Session 2 (48-72 hours postpartum): Review the previously covered knowledge and offer additional skills training aimed at enhancing the mother's confidence. Individualized support is provided to address her specific concerns, lasting about 60 minutes.

- Session 3 (Post-discharge follow-up): Following discharge, the program includes weekly follow-up messages sent via mobile application through the 'Line Official Account™ Parent Paplearn' for five weeks to address any questions or concerns related to challenges faced by the mother or her infant.

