## **11. Data Collection**

### **11.1 Participant Recruitment**

The researcher collaborated with nurses to identify eligible participants who met inclusion criteria and obtained permission to meet them after 24 hours postpartum. During these meetings, the researcher explained the study objectives, procedures, and participants' rights. Informed consent forms were then obtained from the participants.

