## **15. Risk and Investigator's responsibility**

This study does not involve any procedures that present known risks or potential harm to participants. Its primary objective is to provide education and promote parenting competence, supplemented by the completion of questionnaires. Participants may experience fatigue or emotional discomfort during the process. Participation is entirely voluntary; individuals may withdraw from the study at any time or decline to answer any questions without penalty.

In cases where a participant exhibits postpartum complications following hospital discharge, scoring 11 or higher on the EPDS or indicating suicidal thoughts was not excluded. Instead, the researcher provided initial support by actively listening to their concerns and referred them to a nurse who facilitated further consultation with a psychiatrist, ensuring that they received appropriate emotional and mental health care.

If any harm results from participation in the study, appropriate care will be provided immediately. For any injury or to obtain further information regarding the research project, participants may contact the researchers, [name] and Assistant [name]. [name], at Srisavarindhira Thai Red Cross Institute of Nursing, [name]. They can be reached at [contact], available 24 hours.

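### The three exclusion criteria are events that follow enrolment, so the protocol restricts the analysis to completers who stayed personal caregivers, and this can bias the group comparison

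*Protocol*

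**What the plan says.** The protocol's list of exclusion criteria, under section 10.4, has exactly three items:

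- "The participant did not personally care for the infant for the entire six-week postpartum period"
- "The participant was unable to complete all phases of the study"
- "The participant chose to withdraw from the research"

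Recruitment comes much earlier. Section 11.1 says the researcher "obtained permission to meet them after 24 hours postpartum" and took consent at those meetings. The part of the caregiving condition that can be judged at entry is already an inclusion criterion in section 10.4: "Mother intended to childcare for six-week".

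Section 10.3 gives 26 mothers per group, raised to 30 for 10% dropout. Section 12 plans independent t-tests between the groups and names no analysis population. Section 9 describes a quasi-experimental design with a pre-test and a post-test.

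Section 10.6.1 gives the program two in-person sessions and five weeks of follow-up messages. The text sets out no equivalent for standard care; the flow diagram (Figure 3) is not shown. Section 15 says that a mother "scoring 11 or higher on the EPDS or indicating suicidal thoughts was not excluded".

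**The concern.** An exclusion criterion should define who may enter, using facts available at entry. These three define who is removed afterwards. Section 12 does not use the word completers, but a completers' data set follows from the list, and the dropout allowance in section 10.3 fits that reading. Because the rule stands in the protocol itself, it is not a detail left to a statistical analysis plan.

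The removal is plausibly tied to the outcomes. The trial measures parenting stress and parenting competence. A mother who hands over care of her infant, or cannot keep up with the study, may well do so because she is stressed or feels unable to cope. The protocol's own rationale (section 3) links stress and anxiety in adolescent mothers to ineffective caregiving and role conflict. The first criterion also removes mothers whose six-week scores could still be collected.

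Losses could differ by group. If completing all phases includes the program sessions, there is more to complete in the intervention group than the text describes for controls. The design is not described as randomised, so selective loss would add to whatever imbalance exists at entry.

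**Working it through.** **Timing of each criterion**

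| Criterion | When it can be known | Version available at entry |
|---|---|---|
| Personal care for the whole six weeks | At six weeks | Intention to give care, already an inclusion criterion |
| Completing all phases | At the end of the study | None |
| Withdrawal | At any time after consent | None |

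Consent is taken shortly after 24 hours postpartum, so all three come after enrolment.

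**The plan's own figure.** Inputs from section 10.3: power 0.80, significance level 0.05, a large effect. The effect size is not printed and sidedness is not stated; d = 0.8 and a two-sided test are assumed. The noncentral-t calculation for two independent means gives n = 25.52, so 26 per group, matching the protocol. For dropout, 26 / (1 − 0.10) = 28.9, so 29, against 30 stated. The sample size is not in dispute.

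**How large a bias could be.** The documents give no losses by group, so this is an illustration under stated assumptions:

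- no true program effect, and 30 mothers per group;
- 3 lost per group (3/30 = 10%, the planned rate) or 4 lost per group (4/30 = 13.3%, which takes 30 down to 26);
- control losses random;
- intervention losses falling on the mothers with the worst values of a marker that has correlation ρ with the outcome.

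The large-sample shift in the mean of those retained is ρ × φ(z) / (1 − p), where p is the fraction lost and z is the normal quantile at 1 − p.

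- p = 0.10: z = 1.282, φ(z) = 0.1755, 0.1755 / 0.90 = 0.195 SD at ρ = 1.
- p = 0.133: z = 1.111, φ(z) = 0.2153, 0.2153 / 0.867 = 0.248 SD at ρ = 1.

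Simulation at the actual group size (100,000 trials per row) gives slightly smaller shifts:

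| Lost per group | ρ | Bias (SD) | Two-sided false-positive rate |
|---|---|---|---|
| 3 | 0 | 0.00 | 5.1% |
| 3 | 0.3 | 0.06 | 5.6% |
| 3 | 0.5 | 0.09 | 6.6% |
| 3 | 1.0 | 0.19 | 12.4% |
| 4 | 0 | 0.00 | 5.0% |
| 4 | 0.3 | 0.07 | 5.9% |
| 4 | 0.5 | 0.12 | 7.5% |
| 4 | 1.0 | 0.24 | 16.7% |

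Against the assumed d of 0.8, a bias of 0.06 to 0.12 SD is 0.06 / 0.8 = 8% to 0.12 / 0.8 = 15% of the effect planned for. If the same outcome-related loss occurs in both groups and there is no true effect, the two shifts cancel. If control losses are the selective ones and intervention losses are random, the size is the same and the sign reverses.

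**Effect of the fix on power.** Two-sided power at d = 0.8 is 0.807 with 26 per group, 0.822 with 27 (30 less 10%) and 0.861 with all 30.

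**The case against.** Several points on the other side stand.

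*Unequal losses are not shown.* A reader might infer that the rule removes mothers differently in the two groups. The wording is the same for both, no losses by group are given, and the control pathway may be in the figure that is not shown. Phases of the study could also mean the pre-test and post-test, which both groups have; the program's parts are called sessions and activities. On that reading, the second and third items mostly describe mothers with no post-test score. The first item still removes mothers with obtainable scores.

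*The direction is open.* A reader might infer a bias in favour of the program. It is equally possible that unsupported control mothers hand over care or withdraw more often, and removing them would work against the program.

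*Two apparent contradictions are not contradictions.* The second session is placed as follows: "Session 2 (48-72 hours postpartum): Review the previously covered knowledge". Section 3 speaks of "Routine hospital discharge within 2–3 days". These cover much the same period, and section 3 describes general practice, not the discharge times of trial mothers. Section 15 says that a positive depression screen does not in itself exclude a mother, and the exclusion list does not name it. A mother may be kept after a positive screen and lost later for another reason. What remains is ambiguity about how such mothers are analysed.

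*Caregiving may define the target group.* The first item could be meant to confine the question to mothers who actually gave care. Intention at entry already serves that purpose without conditioning on what follows.

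*Imputation is a partial remedy.* If losses depend on stress that arises after baseline, imputing from baseline data does not repair them. This is a reason to put collection of the scores first.

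**Conclusion.** The concern holds as a conditional risk. It is certain from the text that all three exclusion criteria are events after enrolment and that, as written, they restrict the analysis to completers who remained personal caregivers. Whether this biases the comparison depends on two things the documents do not settle: whether losses relate to stress or competence, and whether they differ by group. Both are credible.

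Under the illustration's assumptions the bias is modest at ρ of 0.3 to 0.5: about 0.06 to 0.12 SD, with a false-positive rate of 5.6% to 7.5%. The upper figures, about 0.19 to 0.24 SD and 12% to 17%, need perfect selection on the outcome in one group and random loss in the other. They are an extreme, not an expectation. There is no bias if losses are unrelated to outcome or, with no true effect, if the same outcome-related loss occurs in both groups. The loss rates, correlations, d = 0.8 and two-sidedness are assumptions; the exact match to 26 per group supports the last two.

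**What to change.** 1. Remove the three items from the exclusion criteria and list them as reasons for discontinuation or withdrawal.
2. Seek the six-week stress (PSI-4-SF) and competence (PSOC) scores from every enrolled mother who has not withdrawn consent to data collection, whether or not she completed the sessions or remained the personal caregiver.
3. In section 12, analyse all enrolled mothers in the group they entered, with a stated missing-data method.
4. Report the number lost and the reasons, by group.
5. Keep the completer and personal-caregiver set as a sensitivity analysis.
6. Clarify that a mother discharged before the second session, or one kept in the study under section 15, stays in the analysis. This concerns the analysis only and implies no change to session timing or care.

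The cost is a short amendment to sections 10.4 and 12 and a few extra follow-up contacts, including contacts with controls, for whom the text describes no follow-up channel. Including mothers who received less of the program will dilute the estimated effect somewhat. No larger sample is needed.

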## 5. Objectives

1. Developed a Line Official Account “Parent Paplearn”.
2. To compare parenting stress among postpartum adolescent mothers who participated in the parental enhancing program with the mobile application through ‘Line Official Account™ Parent Paplearn’ and those receiving standard postpartum care.
3. To compare parenting competence among postpartum adolescent mothers who participated in the parental enhancing program with the mobile application through ‘Line Official Account™ Parent Paplearn’ and those receiving standard postpartum care.

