## 9. Research Design

This study employed a quasi-experimental control group pre-post-test design

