## **12. Data analysis and statistics**

IBM SPSS Statistics was used for data analysis, statistical significance was set at  $p < .05$ .

1. Descriptive statistics were used to characterize the participant demographic and obstetric characteristics.

2. The comparison of differences between the characteristics of the intervention group and the control group was conducted using independent t-test, Chi-square test, and Fisher's exact test, based on type of the variables and assumptions of statistical.

3. The dependent t-test was used to determine significant differences in parental stress and competence scores before and after the intervention within each group.

4. The independent t-test was used to determine significant differences in parental stress and competence scores between the intervention group and the control group

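### Exclusion item 2 is a post-enrolment completers rule; if its undefined phases include programme sessions, it can remove intervention mothers but not comparable controls (minor)

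*Protocol*

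**What the plan says.** The second item under the Protocol's Exclusion criteria is: "The participant was unable to complete all phases of the study". Item 1 (not caring for the infant personally throughout the six weeks) and item 3 (withdrawal) are also known only after enrolment. Because withdrawal has its own item, item 2 reaches mothers who are still willing to take part but did not complete something.

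Section 10.6.1 describes the intervention programme. Session 1 is at 24-48 hours. The next is described as "Session 2 (48-72 hours postpartum): Review the previously covered knowledge and offer additional skills training aimed at enhancing the mother's confidence". For the third, "Following discharge, the program includes weekly follow-up messages sent via mobile application", over five weeks. Section 5 describes the comparison group only as "and those receiving standard postpartum care".

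Section 9 states: "This study employed a quasi-experimental control group pre-post-test design". Section 12, item 4, gives the between-group analysis: "The independent t-test was used to determine significant differences in parental stress and competence scores between the intervention group and the control group". Item 3 of that section adds within-group tests before and after the intervention.

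**The concern.** A rule that removes participants for what happens after enrolment changes who is compared. Here it may act unequally. On its plain wording, all phases of the study can include the programme sessions, and only the intervention group has those. An intervention mother who misses Session 2 could be removed, while a control who would have missed it under the same circumstances stays in.

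If mothers who miss a session differ in stress or competence from those who attend, part of that difference enters the estimated programme effect. The t-test in Section 12 has no stated adjustment for this. If excluded mothers are not followed to six weeks, no later choice of analysis set can recover their scores.

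**Working it through.** **Plan's own figure.** Section 10.3 gives 26 per group, raised to 30 for 10% dropout, for a large effect, power 0.80 and alpha 0.05. With d = 0.8 (assumed; the Protocol gives no number) and a two-sided two-sample t-test, n = 25.52, rounded up to 26, which matches. Then 26 / 0.9 = 28.9, or 29, against the stated 30. The sample size is not in dispute.

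**Does the rule act unequally?**

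| Possible phase | Intervention | Control |
|---|---|---|
| Pre-test, post-test | yes | yes |
| Session 1, 24-48 h | yes | none |
| Session 2, 48-72 h | yes | none |
| Weekly messages, five weeks | yes | none |

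The asymmetry lies in the last three rows. Session 1 follows closely on recruitment, which takes place after 24 hours. The weekly messages are sent by the team, and no reply is required in the text. That leaves mainly Session 2, through discharge before it is delivered.

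**Size of bias.** The documents give no count of removals and no outcome difference, so both are assumptions:
- k of the 30 intervention mothers are removed, so p = k/30, with k from 0 to 3. The top value equals the 10% dropout allowance for that arm.
- s is the difference in mean outcome between those who attend and those who miss, 0.2 to 0.8 SD.

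The full-group mean is (1 - p) x (attender mean) + p x (misser mean). The attender mean therefore departs from it by p x s, and this is the bias. The rejection rate with no true effect comes from the noncentral t, two-sided alpha 0.05, 30 - k against 30:

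| k | Bias in SD, s = 0.2 / 0.5 / 0.8 | Type I error |
|---|---|---|
| 0 | 0 | 0.0500 |
| 1 | 0.007 / 0.017 / 0.027 | 0.0501 / 0.0505 / 0.0512 |
| 2 | 0.013 / 0.033 / 0.053 | 0.0503 / 0.0518 / 0.0546 |
| 3 | 0.020 / 0.050 / 0.080 | 0.0506 / 0.0539 / 0.0601 |

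At k = 3 the bias is 0.02/0.8 = 2.5% to 0.08/0.8 = 10% of a d of 0.8. A simulation with 200,000 runs at k = 3 gave bias 0.019 / 0.051 / 0.080 and type I error 0.051 / 0.053 / 0.056, so the table is if anything slightly high.

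**Power if these mothers are kept (d = 0.8, 30 v 30; 0.861 with full benefit for all).**
- 1 of 30 with half the benefit: d = 0.8 x (1 - 0.5/30) = 0.787, power 0.850.
- 3 of 30 with half the benefit: d = 0.8 x (1 - 0.05) = 0.76, power 0.825.
- 3 of 30 with no benefit: d = 0.8 x (1 - 0.10) = 0.72, power 0.783.
- 3 of 30 excluded, 27 v 30: power 0.842.

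**The case against.** The strongest reply concerns the word itself. The Protocol calls the programme components sessions and activities, never phases, and item 2 speaks of the study, not the programme. In a pre-test/post-test design the phases may well be the two assessments. Item 2 would then apply to both groups alike and a missed session would exclude nobody. The flow diagram (Figure 3), which is not shown, may settle this. All of this stands, and it makes the point conditional.

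Three stronger readings are tempting and are not supported:
- **That many mothers would miss Session 2.** Section 3 says "Routine hospital discharge within 2–3 days limits opportunities for comprehensive and continuous skill development", which might suggest routine loss. But Session 2 opens at 48 hours, the start of that usual stay, so a mother with a routine stay is usually still on the ward.
- **That the between-group test ignores the pre-test scores.** Section 12, item 4, does not say whether post-test or change scores are compared. What can be said is that no adjustment for selection on completion is stated. The comparison of group characteristics (item 2) and the pre-test scores offer partial checks.
- **That the rule favours the programme, or does so substantially.** It would favour the programme only if mothers who miss sessions would have scored worse, and nothing in the documents shows this. Simulations with 6 of 30 removed and correlations of 0.3 to 0.5 between completion and outcome give type I error of 0.068 to 0.099, but no text supports such counts.

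Nor are controls immune. They can be removed under item 2 for a missed assessment, and under items 1 and 3. The imbalance concerns session non-completion only.

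It may also be said that analysis sets belong in a statistical analysis plan. That has limited force, because the Protocol itself states the exclusion rule.

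**Conclusion.** The point holds conditionally and is minor. Item 2 is a post-enrolment completers rule on any reading. If phases includes the sessions, it can select the intervention group on completion without a matching selection of controls.

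The direction of any bias is unknown. Its size is probably small: 0.02 to 0.08 SD, with type I error of at most about 0.06, at the upper end of the assumed removals (3 of 30). Both inputs are assumptions. There is no such bias if no mother is removed for a missed session, if missing one is unrelated to the outcomes, or if phases means only the two assessments.

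**What to change.** Reword item 2 so that missing a programme session is not a ground for exclusion. Collect the six-week stress and competence scores from these mothers and analyse them in their own group. If phases was meant as pre-test and post-test only, say so in the item.

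The change to the text is about one sentence. It moves the question from the effect among completers to the effect among all enrolled, with slight dilution. In the least favourable case worked above (3 of 30 with no benefit), power falls below the planned 0.80, to 0.783. With half the benefit it stays above, at 0.825.
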